# Low- versus high-concentration iodine contrast media for coronary computed tomography angiography and dynamic stress computed tomography perfusion: a study protocol for a prospective randomized trial

**DOI:** 10.1186/s44348-026-00082-9

**Published:** 2026-07-24

**Keywords:** Coronary computed tomography angiography, Myocardial perfusion imaging, Contrast media, Equivalence trial, Myocardial blood flow, Clinical Trial Protocol

## Abstract

**Background:**

This prospective randomized study protocol is designed to determine whether low-concentration iodine contrast media can maintain coronary enhancement on coronary computed tomography angiography (CCTA) compared with high-concentration iodine contrast media under standardized acquisition conditions. Dynamic stress computed tomography perfusion (CTP)-derived myocardial blood flow (MBF) will be assessed as a key secondary quantitative endpoint. Exploratory diagnostic performance analyses using invasive coronary angiography (ICA) and fractional flow reserve (FFR) will be performed only in clinically indicated invasive testing subgroups.

**Methods:**

The trial plans to enroll 258 adults (age ≥ 40 years) with known or suspected coronary artery disease referred for clinically indicated cardiac computed tomography, including CCTA with planned dynamic stress CTP. Participants will be randomized 1:1 to receive low-concentration iodine contrast media (270 mg I/mL) or high-concentration iodine contrast media (350 mg I/mL). The primary endpoint is quantitative coronary enhancement on CCTA. Dynamic stress CTP-derived MBF will be evaluated as a key secondary endpoint focused on quantitative comparability. ICA/FFR-based diagnostic performance analyses will be considered prespecified exploratory analyses in participants who undergo invasive testing as part of routine clinical care. The primary endpoint will be analyzed using linear mixed-effects models with a prespecified noninferiority margin, and MBF will be analyzed using mixed-effects models without claiming formal equivalence or noninferiority.

**Discussion:**

This study protocol is expected to clarify whether low-concentration iodine contrast media can maintain CCTA coronary enhancement and support quantitative dynamic stress CTP assessment while reducing iodine exposure. Because ICA and FFR are clinically driven rather than protocol mandated, diagnostic performance analyses will be interpreted cautiously and regarded as exploratory.

**Trial registration:**

CRIS identifier: KCT0011418. Registered on January 7, 2026.

## Background

Coronary computed tomography angiography (CCTA) has become a first-line noninvasive test for evaluating coronary artery disease (CAD), providing high diagnostic accuracy for detecting luminal stenosis and characterizing atherosclerotic plaque [1–3]. Nevertheless, CCTA has important inherent limitations. It offers a predominantly anatomic assessment of the coronary lumen and does not directly quantify the hemodynamic significance of individual lesions; consequently, the correlation between anatomic stenosis severity and functionally significant ischemia is at best modest [4]. Image quality and diagnostic performance may also be substantially degraded in patients with heavy coronary calcification or prior stents, where blooming artifacts can overestimate stenosis and increase false-positive rates [5, 6].

Dynamic stress computed tomography perfusion (CTP) is a functional imaging technique that quantifies the hemodynamic significance of coronary stenosis by measuring myocardial blood flow (MBF) under pharmacologic stress. When combined with CCTA in a single examination, dynamic stress CTP adds functional data to anatomic information, enabling a more comprehensive characterization of CAD than either modality alone and potentially improving diagnostic confidence and clinical decision-making [7–9]. This comprehensive strategy poses a dilemma in contrast use. Although high-concentration iodinated media have been favored to maximize coronary opacification, distal vessel visualization, side-branch conspicuity, and diagnostic confidence, they also increase the total iodine load, an important modifiable factor in patients at risk for contrast-associated acute kidney injury [10–12]. This issue is particularly relevant in patients with renal impairment, diabetes, or cardiovascular comorbidities.

Recent advances in computed tomography (CT) hardware and software have challenged the traditional linkage between iodine concentration and image quality. In particular, low-tube-voltage techniques augment iodine attenuation and may allow diagnostically adequate enhancement with lower iodine concentration while reducing radiation exposure [13–16]. Previous studies have also demonstrated the feasibility of low-concentration or personalized iodine contrast protocols for CCTA [17–19]. However, the ability of a low-concentration iodine protocol to maintain distal coronary visualization, side-branch conspicuity, overall CCTA diagnostic confidence, and dynamic stress CTP interpretability remains to be determined and is a key motivation for the present randomized protocol. Although dynamic stress CTP-derived MBF is primarily a physiology-based quantitative parameter, contrast iodine concentration may influence attenuation amplitude, image noise, arterial input function quality, time-attenuation curves, and post-processing robustness. Therefore, empirical evaluation of MBF comparability between low- and high-concentration iodine protocols is scientifically justified.

For a contrast media optimization protocol intended for clinical translation, technical image quality assessment alone is not sufficient. It is also important to predefine how downstream invasive coronary angiography (ICA) and fractional flow reserve (FFR) data, when obtained as part of routine care, will be analyzed. In the present study, such invasive reference standard analyses are prespecified as exploratory and hypothesis-generating because invasive testing is clinically indicated rather than mandated by the protocol.

## Methods

### Ethics statement

The protocol has been approved by the Institutional Review Board of Wonju Severance Christian Hospital (No. CR122087). The trial will be conducted in accordance with the Declaration of Helsinki and the International Council for Harmonization Good Clinical Practice guidelines. Written informed consent will be obtained from all participants before any study procedures. The trial was registered at the Clinical Research Information Service (CRIS identifier: KCT0011418).

### Trial design

This study protocol describes a prospective, single-institution, randomized, participant-, investigator-, and reader-blinded noninferiority trial (Fig. 1). The primary objective is to evaluate whether a low-concentration iodine contrast protocol is noninferior to a high-concentration iodine protocol for quantitative coronary enhancement on CCTA. Dynamic stress CTP-derived MBF will be evaluated as a key secondary quantitative endpoint focused on comparability. ICA/FFR-based diagnostic performance analyses will be considered prespecified exploratory analyses in clinically indicated invasive testing subgroups.

**Fig. 1 Fig1:**
[figure not shown]
Study flow diagram and design. CCTA, coronary computed tomography angiography; CT, computed tomography; CTP, computed tomography perfusion; FFR, fractional flow reserve; ICA, invasive coronary angiography; MBF, myocardial blood flow

### Population and setting

The trial plans to enroll 258 adults with known or suspected CAD referred for clinically indicated cardiac CT, including CCTA with planned dynamic stress CTP. Eligible participants will be ≥ 40 years of age, will have electrocardiography (ECG)-gated imaging feasibility, and will have adequate renal function (e.g., estimated glomerular filtration rate [eGFR] ≥ 45 mL/min/1.73 m^2^). Exclusion criteria will include suspected acute myocardial infarction or unstable angina; complex congenital heart disease; significant renal dysfunction or acute kidney injury (e.g., serum creatinine ≥ 1.5 mg/dL or eGFR < 45 mL/min/1.73 m^2^); history of coronary artery bypass grafting (percutaneous coronary intervention/stents permitted and recorded); pregnancy or lactation; history of severe hypersensitivity to iodinated contrast media or vasodilator stress agents; contraindications to nitroglycerin; contraindications to adenosine triphosphate; and uncontrolled arrhythmia precluding diagnostic acquisition. Eligible participants will be recruited from the routine clinical cardiac CT population at our institution during the planned study period.

### Sample size

The sample size is based on the primary noninferiority endpoint for CCTA enhancement. Based on prior data indicating approximately a 10.77% reduction in ascending aortic attenuation with low- versus high-concentration contrast, the noninferiority margin is set at 11% (approximately 50 Hounsfield units [HU]) [14, 15]. Assuming a standard deviation (SD) of 119 HU, one-sided α = 0.025 and 90% power, 117 participants per group are required. Allowing for 10% attrition, the target enrollment is 129 participants per group (total, n = 258). Secondary MBF and exploratory diagnostic performance analyses will be interpreted in light of the available analyzable data and the number of participants undergoing clinically indicated invasive testing.

A formal pilot study was not performed, which may limit the precision of feasibility estimates before completion of the trial. However, the protocol was developed based on prior low-iodine CCTA studies and institutional experience with integrated CCTA and dynamic stress CTP, and recruitment feasibility will be monitored throughout the study period.

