### Contrast media and injection protocols

Participants will receive either high-concentration iodine contrast media (iobitridol 350 mg I/mL; Xenetix 350, Guerbet) or low-concentration iodine contrast media (iohexol 270 mg I/mL; Iobrix 270, Taejoon Pharmaceutical). Dynamic stress CTP will use a fixed volume of 40 mL injected at 5 mL/sec followed by a 30 mL saline chaser in both groups. Therefore, under otherwise identical perfusion-acquisition conditions, the dynamic stress CTP analysis specifically tests whether iodine concentration affects quantitative MBF measurement and interpretability.

CCTA will use a triphasic protocol at 4.5 mL/sec: 0.9 mL/kg of the assigned contrast media, followed by 45 mL of a 70:30 saline-to-contrast mixture (70% saline and 30% contrast medium), and a final 30 mL saline chaser. Two intravenous lines will be secured for contrast media injection and adenosine triphosphate infusion. All injections will be performed with a dual-head power injector (Dual Shot GX7, Nemoto Kyorindo). Weight-based dosing and fixed scan timing are intended to standardize iodine delivery conditions across participants.

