### CT reconstruction and post-processing

Dynamic stress CTP datasets will be reconstructed in the axial plane (slice thickness 3 mm, 2 mm overlap) using a medium-sharp quantitative kernel (Qr40, Siemens Healthineers) to preserve linearity of iodine attenuation. Post-processing will be performed on a workstation (Syngo.via VB10, Siemens Healthineers) using commercial perfusion software. MBF (milliliters per 100 mL/min) will be derived by parametric deconvolution based on a two-compartment tracer-kinetic model applied to time-attenuation curves. The arterial input function will be placed in the ascending aorta or left ventricular cavity using standardized regions of interest (ROIs). The left ventricle will be segmented according to the American Heart Association (AHA) 17-segment model and polar maps generated for territorial and segmental analyses.

CCTA datasets will be reconstructed with a medium-soft vascular kernel (Bv40, Siemens Healthineers) and iterative reconstruction (ADMIRE strength 3, Siemens Healthineers). Images will be transferred to an offline workstation for post-processing, and optimal phases (mid-diastolic and/or end-systolic) will be selected for evaluation. Dynamic stress CTP and CCTA acquisition parameters, including tube-voltage strategy, ECG-gating approach, reconstruction kernel, slice thickness, and iterative reconstruction settings, will be applied identically in both contrast groups to support reproducibility and minimize confounding by scan parameters.

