### Statistical methods

All statistical analyses will be performed using SAS ver. 9.4 (SAS Institute Inc). Baseline characteristics will be summarized by group. Standardized mean differences (SMDs) will be used to assess baseline balance; variables with absolute SMD ≥ 0.25 will be considered imbalanced and included as covariates in sensitivity analyses.

Quantitative endpoints with repeated measures (HU, SNR, CNR, and MBF) will be analyzed using linear mixed-effects models with random intercepts for patients to account for intraindividual correlation across vessels or myocardial segments. Fixed effects will include contrast group, measurement location, and group × location interaction where appropriate. For the primary CCTA enhancement endpoint, noninferiority will be assessed using the estimated between-group difference (low minus high) and its two-sided 95% confidence interval. Noninferiority will be concluded if the lower bound of the 95% confidence interval for ΔHU is greater than –50 HU and if diagnostic adequacy criteria are met.

For the key secondary MBF endpoint, between-group differences will be estimated using a linear mixed-effects model. Because no clinically justified noninferiority or equivalence margin is prespecified for MBF, the analysis will be interpreted as an assessment of quantitative comparability rather than formal equivalence or noninferiority. A nonsignificant between-group difference will not be interpreted as proof of equivalence.

Qualitative image quality endpoints (Likert scores) will be compared using Mann–Whitney U-tests, with proportional-odds models as sensitivity analyses. Interobserver agreement will be assessed using weighted kappa for ordinal scales and Cohen κ for binary acceptability.

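### The 90% power holds only if the true coronary HU difference is about zero; this is neither stated nor justified, and it conflicts with the only effect cited, a 10.77% loss

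*Protocol article*

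**What the plan says.** The Sample size section cites earlier studies, "Based on prior data indicating approximately a 10.77% reduction in ascending aortic attenuation with low- versus high-concentration contrast", and on that basis sets the margin at 11%, which it equates with about 50 HU. The calculation follows: "Assuming a standard deviation (SD) of 119 HU", then "one-sided α = 0.025 and 90% power, 117 participants per group are required". With a 10% allowance for attrition, the target is 129 per group, 258 in total. The section does not name the true between-group difference at which the power was computed.

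Statistical methods applies the same limit. The claim requires that the lower bound of "the 95% confidence interval for ΔHU is greater than –50 HU and if diagnostic adequacy criteria are met".

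Contrast media and injection protocols gives both arms "0.9 mL/kg of the assigned contrast media" at 4.5 mL/sec for CCTA, with iodine at 350 or 270 mg I/mL. CT reconstruction and post-processing says that acquisition parameters, including the tube-voltage strategy, "will be applied identically in both contrast groups to support reproducibility and minimize confounding by scan parameters".

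**The concern.** A power figure for a noninferiority test has meaning only at a stated true difference. The paragraph states none. The one effect size it does cite lies almost on the margin, so the prior loss shapes the margin but plays no visible part in the power.

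This is the primary test. A reader who takes 90% power at face value will think the trial very likely to succeed unless the low-concentration protocol is truly unacceptable. If there is a real coronary loss of even 20 HU, well inside the margin, the chance of showing noninferiority is about one in two. A failed test would then say little about whether the loss exceeds the margin, and the published power would hide this.

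**Working it through.** **Inputs (all from Sample size):** SD 119 HU; margin M = 50 HU, said to be about 11%; one-sided α = 0.025 (z = 1.960); power 90% (z = 1.282); n = 117 per group, allocated 1:1; prior loss 10.77% in the ascending aorta.

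**1. Reproduce the plan's figure.** With true difference 0:

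n = 2 × (119 × (1.960 + 1.282) / 50)² = 119.04, so 120 per group after rounding up.

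This is within 3% of the stated 117. The small gap is no part of this point. In the other direction:

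SE = 119 × √(2/117) = 15.56 HU
Power = Φ(50/15.56 − 1.960) = Φ(1.254) = 89.5% (89.3% with the noncentral t)

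The stated n and power therefore correspond to a true difference of about zero. Changing other inputs does not give 117: 80% power gives 89 per group, and one-sided α of 0.05 gives 98.

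**2. Power at a nonzero loss d:** Φ((50 − d)/15.56 − 1.960)

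| True loss d (HU) | Power, 117 per group |
|---|---|
| 0 | 89.5% |
| 10 | 73% |
| 20 | 49% |
| 30 | 25% |
| 40 | 9% |
| 48.95 (cited 10.77%) | 2.9% |

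The last row uses the article's own conversion. The reference mean is 50/0.11 = 454.5 HU, and 0.1077 × 454.5 = 48.95 HU, which is 1.05 HU inside the limit. Power is Φ(1.05/15.56 − 1.960) = 2.9%. It is also 2.9% with all 129 per group evaluable.

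**3. Sensitivity of the last row.** The article gives no reference mean, so 400 to 500 HU is assumed, with the margin fixed at 50 HU:

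| Assumed reference mean (HU) | 10.77% loss (HU) | Power |
|---|---|---|
| 400 | 43.08 | 6.5% |
| 450 | 48.47 | 3.1% |
| 460 | 49.54 | 2.7% |
| 500 | 53.85 | 1.4% |

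The SD hardly matters here. An assumed SD of 80 HU gives 3.1% and 60 HU gives 3.4%, because the distance to the margin is so small. At intermediate losses the SD does matter, so those powers hold for the article's 119 HU.

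**4. Is zero difference supported elsewhere?** The CCTA volume rule (0.9 mL/kg) and rate (4.5 mL/sec) are the same in both arms. Iodine delivery in the low arm is thus 270/350 = 0.771 of that in the high arm, or 22.9% lower. Background names low tube voltage as a technique that may allow adequate enhancement with less iodine. CT acquisition protocol and CT reconstruction and post-processing apply the same tube-voltage strategy to both arms, so no arm-specific compensation is planned. The article gives no other reason to expect equal coronary attenuation.

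**The case against.** **Zero difference is a common planning assumption for noninferiority.** It is, and using it is not in itself an error. But it should be stated, and here it needs a reason, because the only effect cited in the same paragraph is almost as large as the margin.

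**The protocol does not say that it expects a 10.77% loss.** This stands. The figure is cited as prior data and used only to set the margin. A reader might infer that the trial plans for this loss and is almost certain to fail. The article does not support that. The figure is for the ascending aorta, while the endpoint is measured in proximal and distal coronary segments (Image analysis). Tube voltage and injection conditions in the cited studies cannot be seen from this article. The 3% is the power in one scenario, not the known power of the design. Still, the protocol itself carries the aortic figure over to set a coronary margin, so it cannot be dismissed as irrelevant to power.

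**Larger claims are tempting.** A reader might scale attenuation by the 22.9% lower iodine delivery. That assumes strict proportionality, which the article does not state, and the one loss it cites is less than half as large. A reader might also compute the sample size needed for 90% power at the cited loss. That number is not usable: it rests on a gap of about 1 HU between two approximate figures, and runs from about 126,000 per group at a reference of 450 HU to about 930,000 at 459 HU.

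**The confidence interval is informative whatever the verdict.** Also true. ΔHU with its 95% interval is already the prespecified primary analysis, so nothing needs to change there.

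**A separate analysis plan may cover this.** The article gives the sample-size derivation itself. The point concerns a stated power figure and its fit with the evidence stated beside it.

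**Conclusion.** The point holds. The stated 90% power is conditional on a true difference of about zero (89.5% at 117 per group). That condition is neither stated nor justified, and nothing in the article supports it. Power falls to about 73%, 49% and 25% at true losses of 10, 20 and 30 HU. It is about 3% if the cited 10.77% loss applies to coronary HU at the implied reference of about 455 HU, with a range of 6.5% to 1.4% for assumed reference means of 400 to 500 HU. These figures rest on the article's SD of 119 HU and margin of 50 HU; the 3% also rests on the transfer from aorta to coronaries. The further requirement that diagnostic adequacy criteria be met can only lower the chance of concluding noninferiority. The text should be corrected, because the figure concerns the primary test and the change is cheap.

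**What to change.** In Sample size:

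- State that the calculation assumes a true low-minus-high difference of zero.
- Replace the unconditional 90% with power at 117 per group for a true loss of 0 (89.5%), 10 (73%), 20 (49%) and 30 HU (25%), and for the cited 10.77% loss (about 3%).
- Say that the 10.77% was measured in the ascending aorta, and that applying it to coronary HU is an assumption.
- State that failure to show noninferiority is likely if a loss of that size holds in the coronaries.

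The cost is a rewritten paragraph and a less favourable stated power. No extra patients are needed, and the margin, endpoint and primary analysis stay as they are. Whether an 11% loss is a suitable margin is a separate question.

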### Randomization, allocation concealment, and blinding

Participants will be allocated 1:1 to the low- or high-concentration iodine contrast group using a computer-generated allocation protocol prepared by the Department of Preventive Medicine. The allocation sequence will be concealed from the principal investigator, research personnel involved in recruitment and endpoint assessment, participants, image readers, and outcome assessors. The principal investigator and research investigators will not know which contrast concentration is assigned at the time of patient enrollment, image analysis, or endpoint assessment. CT technologists involved in contrast preparation and injection may be aware of the assigned contrast media because the preparations differ; however, they will not participate in patient selection, randomization, image interpretation, endpoint assessment, statistical analysis, or clinical decision-making. After acquisition, CT images will be uploaded to PACS without visible contrast-group identifiers. The principal investigator, research investigators, image readers, and outcome assessors will analyze the anonymized imaging datasets in a blinded arrangement, and the final analytic dataset will be linked to the randomized allocation list only after blinded image analysis is complete. Participants will also not be informed of their assigned contrast concentration. Therefore, the study is described as participant-, investigator-, and reader-blinded, with transparent acknowledgement of technologist unblinding during contrast preparation.

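### Minor sample-size arithmetic: 129 per group after 10% attrition leaves about 116, not 117, and 117 fits a margin of about 50.4 HU rather than the tested −50 HU

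*Protocol article*

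**What the plan says.** The relevant text is in three sections of the protocol article.

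- **Sample size.** The section opens with "The sample size is based on the primary noninferiority endpoint for CCTA enhancement". It gives the margin as "the noninferiority margin is set at 11% (approximately 50 Hounsfield units [HU"]), then continues "Assuming a standard deviation (SD) of 119 HU" and "one-sided α = 0.025 and 90% power, 117 participants per group are required". Enrolment follows in the next sentence: "Allowing for 10% attrition, the target enrollment is 129 participants per group", 258 in total.
- **Randomization, allocation concealment, and blinding.** "Participants will be allocated 1:1 to the low- or high-concentration iodine contrast group".
- **Statistical methods.** The confidence-interval part of the noninferiority criterion is that the "lower bound of the 95% confidence interval for ΔHU is greater than –50 HU".

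The article states neither the true difference assumed in the calculation nor the formula used for attrition.

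**The concern.** The sample-size paragraph makes two linked statements: 117 evaluable per group are needed, and 129 enrolled per group allow for a 10% loss. A reader who repeats the calculation runs into two small mismatches. First, removing 10% of 129 does not leave 117. Second, the stated SD, error rate and power, combined with the −50 HU limit actually used in the test, do not give 117. Both mismatches make the required number look smaller. At stake is whether the stated 90% power follows from the plan's own inputs and decision rule.

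**Working it through.** **Inputs.** From Sample size: SD 119 HU, margin 11% or approximately 50 HU, one-sided α 0.025, power 90%, attrition 10%. From Randomization: 1:1 allocation. From Statistical methods: test limit −50 HU. The assumption added here is a true difference of zero. The protocol does not state it, but it is the value that brings the formula close to 117.

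**Step 1: reproduce 117.** For two means with a noninferiority margin M and zero true difference,

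n per group = 2 × (z₀.₉₇₅ + z₀.₉₀)² × (SD/M)².

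At M = 50: 2 × (1.95996 + 1.28155)² × (119/50)² = 119.04, so 120 per group. With z rounded to 1.96 and 1.28 the result is 118.9, so rounding of z does not explain 117. The noncentral t-distribution needs 121, because power at 120 is 89.999%.

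Solving for the margin that gives 117: M = 119 × √(21.015/117) = 50.43 HU, where 21.015 = 2 × (1.95996 + 1.28155)². So 117 is reproduced by a margin of about 50.4 HU.

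**Step 2: reproduce 129.**

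- 117 × 1.1 = 128.7, rounded up to 129, which is the stated figure.
- 117/0.9 = 130, the enrolment that retains 117 after a 10% loss.
- 129 × 0.9 = 116.1, so about 116 remain.
- The largest loss from 129 that still leaves 117 is 12/129 = 9.3%.

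**Step 3: power at the plan's own numbers** (margin exactly 50 HU, SD 119, one-sided 0.025, zero true difference).

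| Evaluable per group | Normal | Noncentral t |
|---|---|---|
| 116 (129 less 10%) | 89.3% | 89.0% |
| 117 (stated requirement) | 89.5% | 89.3% |
| 120 | 90.2% | 90.0% (89.999%) |
| 121 | 90.5% | 90.2% |
| 129 (no loss) | 92.1% | 92.0% |

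**Step 4: enrolment if the steps are corrected.**

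- Attrition alone: 130 per group, 260 in total, 2 more than 258.
- Both steps: 120/0.9 = 133.3, so 134 per group (268 in total); or 121/0.9 = 134.4, so 135 per group (270 in total). That is 10 to 12 more than 258.

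**The case against.** The strongest defence has four parts.

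1. The margin is set as a percentage, and 50 HU is labelled approximate. A sizing margin of 50.4 HU is consistent with that wording, so 117 need not be a miscalculation. **This stands.** It explains how 117 may have arisen. It does not make 117 the number needed for a test against exactly −50 HU.

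2. Multiplying by 1.1 is a common, looser way to allow for 10% attrition, and it costs one participant per group. **The size stands.** Going from 117 to 116 costs about 0.2 to 0.3 points of power. Even so, the stated 129 does not retain the stated 117 at the stated 10% loss.

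3. The gap lies within the uncertainty of the inputs. With 116 per group the normal formula returns 90% if the SD is 117.5 HU instead of 119 HU, and the protocol reports no pilot study. **This stands.**

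4. The planned analysis is a linear mixed model on several coronary measurements per patient, so a two-sample formula with one SD is only a planning approximation. **This also stands.** A one-point difference says little about how the trial will perform, but it is still the calculation from which the article's figures are presented as following.

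A reader might go further and infer that 117 is plainly wrong, or that 258 leaves the trial underpowered. The documents do not support either reading. The first requires treating an approximate figure as exact. The second turns about one percentage point of power, under an assumed true difference, into a design failure.

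**Conclusion.** The point holds as a minor error in stated figures. On attrition the inconsistency is internal and needs no added assumption: 10% off 129 leaves about 116, one below the stated 117. On the base number, the margin that fits 117 (about 50.4 HU) and the margin tested (exactly 50 HU) differ slightly. At the tested margin, 120 (normal) or 121 (t) per group are needed for 90% power.

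Together these put power at 89.0% to 89.3% after 10% attrition, a shortfall of 0.7 to 1.0 points. With no losses, 129 per group would exceed 90%. The trial is not threatened.

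The power figures rest on SD 119 HU, one-sided 0.025, a two-sample comparison, and a true difference of zero. They cover the confidence-interval criterion only, not the added diagnostic adequacy condition. A true deficit in the low-concentration group would require more than 120 per group, so the assumed difference should be stated. Which value is realistic is a separate question that this arithmetic does not settle.

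**What to change.** Keep 258 and revise the Sample size paragraph to:

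- state the exact margin in HU used for sizing, matching the −50 HU limit in Statistical methods, and the true difference assumed;
- give 120 (normal) or 121 (t) evaluable per group as the number needed for 90% power at a 50 HU margin, SD 119 HU, one-sided 0.025 and zero true difference;
- say that 129 enrolled per group with 10% attrition leave about 116 evaluable, giving about 89% power (89.3% normal, 89.0% t) under the same assumptions.

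The cost is a sentence or two and a slightly less favourable stated power. Recruitment, analysis and decision rule do not change.
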